### Work up

Patients with pathologically documented nodal FL Who grade 1 or 2 in stage I or II receive a complete work-up including, cervical, thoracic, abdominal and pelvic CT scans, bone marrow histology and extensive laboratory testing. An ENT examination is mandatory for supra diaphragmal disease and a kidney function test for abdominal disease. The FLIPI risk score will be calculated for each patient. All in- and exclusion criteria are examined. In the event of patients meeting the required inclusion criteria, information about participation in the study with possible risks and benefits is given to the patients and written informed consent is obtained. In the event of patients declining treatment within the MIR trial, irradiation alone is offered.

### Treatment

The treatment lasts over 12 weeks and is divided in 3 sections as illustrated in Figure 1. The first section consists of 4 weekly i.v. infusions of Rituximab (Roche AG, Basel, Switzerland) at a standard dosage of 375 mg/m^2 ^given on day 1, 8, 15 and 22. There is a 4 week treatment break thereafter (week 5 - 8) which includes a radiation therapy planning CT of the involved body region in week 7. Response to the Rituximab therapy is also evaluated at this time. Another 4 weekly infusions of Rituximab are administered in week 9-12. At the same time, radiation therapy of the involved lymph node region is applied, a three dimensional radiation planning is compulsory for all patients having abdominal or retroperitoneal disease. Involved field irradiation consists of a dose of 30 Gy in daily fractions of 2 Gy (Monday to Friday). Patients who still show enlarged lymph nodes in week 7 receive additional boost irradiation with a total dose of 40 Gy. Accepted tolerance doses of organs at risk must not be exceeded.

**Figure 1 F1:**
[figure not shown]
**Study Schema of the MIR trial (IF = involved-field; f/u = follow up)**.

### Safety and discontinuation of treatment

Toxicities are classified by grade, type, duration, onset, and relationship to study treatment.

Treatment of Rituximab-induced adverse reactions is carried according to recommendations by the provider. All patients will receive anti allergic prophylaxis (paracetamol, clemastin) and when appropriate, corticosteroids. In the case of fever (> 38,5°C), chills, bronchial constriction, hypotension (> 30 mm Hg) it is recommended to discontinue treatment with Rituximab.

Analysis of safety related data is performed with respect to frequency of:

• Serious Adverse Events and Adverse Events stratified by organ-system

• Adverse Events stratified by severity

• Adverse Events stratified by causality.

Patient toxicities will be assessed using the NCI Common Toxicity Criteria (CTC). Toxicity will be evaluated prior to treatment, weekly prior to each course of infusional Rituximab and at follow-up. Unacceptable toxicity is defined as unpredictable, or irreversible Grade 4 toxicity. Decisions regarding Rituximab dose-adjustment will be made using the guidelines below and based on haematological parameters (ANC and platelets) monitored weekly during radiation before each dose of Rituximab.

Whenever necessary, metoclopramide or 5-HT_3_-antagonists are used for antiemesis.

Antihistamines such as clemastine are administered prior to Rituximab application.

### Trial duration

Patient recruitment is planned to be completed after 24 months. Patients will be monitored for two and a half years after study entry. The total duration of the trial is estimated to be 4 and a half years. Recruitment started in March 2008. As of February 2010, 65 patients have been included in the trial.

Individual exclusion criteria are serious adverse reactions or the patient's voluntary withdrawal from the trial.

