### Study design and endpoints

The MIR study is a prospective phase II study combining systemic Rituximab therapy with involved field irradiation in patients with FL WHO Grad 1 and 2 in Stage I and II.

This trial aims at testing the combination's efficacy and toxicity with an accrual of 85 patients.

Primary endpoint of the study is progression free survival (2 years). Secondary endpoints are complete remission rate after Rituximab monotherapy (week 7) and after complete treatment (week 18), relapse rate, relapse pattern, relapse free survival, overall survival, toxicity and quality of life.

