### Statistical Design

The hypothesis states an improvement of the progression free survival after 2 years from 75% to 89% (risk reduction by 40% using Rituximab). 77 patients have to be evaluated to proof the hypthesis with a 95% power using a single arm binomial test. An additional 8 patients have to be recruited for a possible 10% drop-out rate.

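### Serious adverse reactions are a ground for individual exclusion and the test is sized on evaluated patients, so patients can be lost from the 2-year PFS test for a treatment-related reason

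*Protocol article*

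**What the plan says.** The exclusion sentence stands in the protocol article under Trial duration, after the statement that patients are monitored for two and a half years from entry. Its operative words are "Individual exclusion criteria are serious adverse reactions"; in full it reads: "Individual exclusion criteria are serious adverse reactions or the patient's voluntary withdrawal from the trial". Entry criteria are given separately under Patient selection, so this is a rule for patients already in the trial.

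Statistical Design sets the hypothesis, "The hypothesis states an improvement of the progression free survival after 2 years from 75% to 89% (risk reduction by 40% using Rituximab", and the size, "77 patients have to be evaluated to proof the hypthesis with a 95% power using a single arm binomial test". It continues: "An additional 8 patients have to be recruited for a possible 10% drop-out rate". Study design and endpoints gives the total of 85 and the endpoint, "Primary endpoint of the study is progression free survival (2 years".

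Safety and discontinuation of treatment names reactions for which stopping rituximab is recommended. It has toxicity assessed before treatment, before each infusion and at follow-up. It then says "Analysis of safety related data is performed with respect to frequency of" serious adverse events and adverse events, broken down by organ system, severity and causality.

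**The concern.** Stopping a drug and leaving a trial are different events, and the article treats them in different sections. Reactions that may lead to stopping rituximab are under Safety and discontinuation of treatment. The exclusion sentence is under Trial duration, next to the monitoring period, and pairs serious adverse reactions with withdrawal from the trial itself. Its natural reading is that the patient leaves the trial.

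A binomial test of 2-year PFS needs a known status at month 24. Treatment lasts 12 weeks, while whole-trunk imaging runs from month 6 to month 30. A patient excluded for a reaction during treatment would have no later scan and no follow-up toxicity visit, and may have received incomplete therapy. Such patients cannot be assumed to be a random tenth of the cohort. In a single-arm trial there is also no comparator subject to the same selection.

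At stake are the error rate of the primary test and the completeness of late toxicity data, in a trial that states both efficacy and toxicity as its aims. Whether follow-up continues is a matter of conduct: a later analysis plan cannot recover scans that were never taken.

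**Working it through.** **Inputs.** From Statistical Design: p0 = 0.75, p1 = 0.89, power 95%, 77 evaluated, 8 extra. From Study design and endpoints: 85 in total. Alpha and sidedness are not stated in the article; one-sided 0.05 is assumed because it reproduces the plan's figure.

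**The plan's own figure.** With the normal approximation,

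n = [(z_α √(p0(1−p0)) + z_β √(p1(1−p1))) / (p1 − p0)]² = [(1.645 × 0.4330 + 1.645 × 0.3129) / 0.14]² = 76.8, so 77.

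Two-sided 0.05 gives 94.8, which does not match. For drop-out, 77 × 1.1 = 84.7, so 85. The sample-size arithmetic therefore reproduces.

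**Decision rule.** The exact binomial rule is the smallest r with P(X ≥ r | n, 0.75) ≤ 0.05. For n = 77 it is r = 65, with actual alpha 3.3% and power 92.3% at 89%.

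**Effect of omitting k of 85.** Let true 2-year PFS be 75% in all 85 (the null), and let the k omitted patients fail at rate f. PFS in those evaluated is

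p = (85 × 0.75 − k(1 − f)) / (85 − k).

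For k = 8 and f = 0.5: (63.75 − 4) / 77 = 0.776. The false-positive rate is P(X ≥ r | 85 − k, p).

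| Omitted (rule) | Quantity | f = 25% | f = 50% | f = 75% | f = 100% |
|---|---|---|---|---|---|
| 8 (≥65/77) | apparent PFS | 75.0% | 77.6% | 80.2% | 82.8% |
| 8 (≥65/77) | false positive | 3.3% | 9.3% | 21.9% | 42.3% |
| 4 (≥68/81) | false positive | 3.7% | 6.2% | 10.0% | 15.4% |
| 2 (≥70/83) | false positive | 2.9% | 3.8% | 4.9% | 6.3% |

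The f = 25% column is the no-bias case: omitted patients fail like everyone else, and the rate is the rule's own alpha.

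**All 85 followed.** The exact rule is ≥71/85, with alpha 4.1% and power 95.6% at 89%.

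**Does censoring solve it?** In a simulation under the null (20,000 runs, log-log confidence interval, one-sided 0.05), 8 such patients were censored in a Kaplan-Meier analysis before the month-6 scan. For f = 50/75/100%, estimated PFS was 77.6/80.2/82.8% and the false-positive rate 9.0/22.0/42.1%. That is essentially the same as leaving them out.

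**Counting leavers as failures.** If all 8 are failures and the other 77 have 89% PFS, the expected rate is 77 × 0.89 / 85 = 80.6%, and power under ≥71/85 falls to about 30%. This suits a sensitivity analysis, not the primary one.

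**The case against.** The strongest reply is that the article nowhere defines the PFS analysis set. Adding 8 patients for drop-out is ordinary inflation, and analysis sets are commonly left to the full protocol or the analysis plan. The exclusion sentence does not say that scans stop or that collected data are discarded, and the two-and-a-half-year monitoring statement just before it carries no exception. This stands to the extent that nobody can say the PFS analysis is restricted to completers, only that the wording allows it. It does not remove the point, because the wording in question is a stated rule and not an omission, and it governs data collection.

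A reader might go further and infer three things that the article does not support:

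- That toxicity is estimated only in patients who got through treatment. The safety section counts serious adverse events, so the triggering reaction is recorded. Only later toxicity is at risk, and only if follow-up stops.
- That drop-outs are replaced. The text describes a 10% increase fixed in advance.
- That PFS is biased upward by a known amount. Direction and size depend on outcomes that the article does not give. The 8 are a possible figure for all drop-out, including voluntary withdrawal, and no rate of serious reactions is stated. The 42.3% is the extreme case; with 2 patients omitted, 5% is exceeded only if nearly all of them fail.

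**Conclusion.** The concern holds as a risk created by two stated rules taken together: an exclusion ground tied to the treatment, and a test sized on evaluated patients. It is not shown that the primary analysis will be biased. Under the null, the apparent gain in 2-year PFS runs from 0 to 7.8 percentage points if all 8 allowed drop-outs are omitted, and the false-positive rate from 3.3% to 42.3%. With 4 omitted, the rate passes 5% once half or more of them fail. These figures assume one-sided alpha 0.05, the exact rule, a true rate of 75% in all 85, and no follow-up of the omitted patients. There is no bias if exclusions are unrelated to outcome, or if excluded patients are still followed and counted. The point merits correction because the wording is easily settled and the lost data could not be recovered afterwards.

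**What to change.** 1. Reconcile the exclusion sentence under Trial duration with the section Safety and discontinuation of treatment, so that leaving treatment and leaving the trial are kept apart. This asks for no rule on when treatment stops; that remains a clinical decision.
2. State that exclusion for a serious adverse reaction does not end imaging, survival or toxicity follow-up, which continues to month 30 unless the patient withdraws consent to follow-up.
3. Analyse PFS and safety in all patients who started therapy.
4. For patients who still leave without a month-24 status, do not rely on censoring alone. Add a sensitivity analysis that counts those who left for toxicity as failures.

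The cost is a change of wording, a few more routine visits, and a PFS estimate that may be slightly lower. The planned 85 patients suffice.

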### Assessment of therapeutic efficiency

CT or MRI of the involved regions are scheduled for week 7 and 18. For screening of the whole body stem, CT or MRI imaging is planned for months 6, 12, 18, 24 and 30 after start of therapy. At all above mentioned follow-up visits, there is also a clinical examination with palpation of all lymph node sites schedulded.

Local response is evaluated in accordance with the Cheson Criteria [30].

• **Complete response (CR) **is the complete disappearance of all detectable evidence of disease on CT, and all disease-related symptoms, and normalization of biochemical abnormalities, and normal bone marrow biopsy (BMB). Previously involved nodes on CT more than 1.5 cm in their greatest axial diameter must regress to less than 1.5 cm, and previously measured nodes of 1.1-1.5 cm must decrease to less than 1 cm.

• **CRu (uncertain) **corresponds to CR criteria but with a residual mass more than 1.5 cm in greatest axial diameter that has regressed by more than 75%.

• **Partial response (PR) **is at least 50% reduction in the sum of the product of the greatest diameters (SPD) of the six largest nodes with no increase in the size of other nodes and no new sites of disease. Splenic and hepatic nodules must regress by at least 50% in the SPD.

• **Stable disease (SD) **is less than a PR but is not progressive disease. Progressive disease (PD) is more than 50% increase in the sum of the product of the greatest diameters of any previously abnormal node, or appearance of any new lesions during or at the end of therapy.

• **Relapsed disease (RD) **is the appearance of any new lesion or increase in size of more than 50% of previously involved sites or nodes in patients who achieved CR or CRu.

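### The CR and CRu size limits leave a residual node of exactly 1.5 cm in neither category, so a slightly larger residual can score better

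*Protocol article*

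**What the plan says.** All of this is in the Protocol article. Under Assessment of therapeutic efficiency, CR requires that nodes "more than 1.5 cm in their greatest axial diameter must regress to less than 1.5 cm". A second clause covers smaller nodes: "previously measured nodes of 1.1-1.5 cm must decrease to less than 1 cm". CRu is CR "with a residual mass more than 1.5 cm in greatest axial diameter that has regressed by more than 75" per cent. PR needs at least a 50% fall in the sum of the products of the diameters, and anything less that is not progression is stable disease (SD). The relapsed-disease category is open only to patients who reached CR or CRu. The section states that local response follows a cited published standard.

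Under Study design and endpoints, the secondary endpoints include the "complete remission rate after Rituximab monotherapy (week 7) and after complete treatment (week 18"), relapse rate and relapse free survival. The primary endpoint is stated separately: "Primary endpoint of the study is progression free survival (2 years").

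**The concern.** Both limits at 1.5 cm are strict, one below and one above, so the value between them belongs to neither category. Such a node drops past CRu to PR or SD. A residual one millimetre larger can still qualify as CRu, so a patient with less disease and more regression can be ranked lower. An ordered response scale should not do that.

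The categories feed named secondary endpoints: the complete remission rate at two time points and, through the relapsed-disease definition, the relapse outcomes. The Discussion also proposes remission state after Rituximab alone as a possible risk factor for recurrence. A boundary patient at week 7 could enter that comparison in the wrong group.

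**Working it through.** **Inputs** (Protocol article)
- CR, node above 1.5 cm at baseline: residual d < 1.5 cm (Assessment of therapeutic efficiency).
- CRu: d > 1.5 cm and regression above 75% (same section).
- PR: reduction of at least 50% in the sum of products (same section).
- Largest eligible tumour: 7 cm (Patient selection).
- 77 evaluable patients, plus 8 for drop-out, giving 85 (Statistical Design).

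The article states no response rate, so there is no figure of its own to reproduce on this point.

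**1. Coverage.** The CR limit admits d < 1.5 and the CRu limit admits d > 1.5. Together they cover every residual except d = 1.5. This holds whatever the baseline size.

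**2. Order.** Take one node of baseline diameter b whose two diameters shrink in proportion, with every other CR condition met. The article does not say how CRu regression is measured. On area it is 1 − (d/b)².

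| Baseline | Residual | Regression on area | Literal category |
|---|---|---|---|
| 4.0 cm | 1.4 cm | 1 − 0.1225 = 87.8% | CR |
| 4.0 cm | 1.5 cm | 1 − 0.1406 = 85.9% | PR |
| 4.0 cm | 1.6 cm | 1 − 0.1600 = 84.0% | CRu |
| 2.5 cm | 1.4 cm | 1 − 0.3136 = 68.6% | CR |
| 2.5 cm | 1.5 cm | 1 − 0.3600 = 64.0% | PR |
| 2.5 cm | 1.6 cm | 1 − 0.4096 = 59.0% | PR |

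From 4.0 cm the order is broken: 1.5 cm ranks below 1.6 cm. From 2.5 cm it is not, because 1.6 cm fails the 75% requirement.

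**3. When the inversion occurs.** A 1.6 cm residual is CRu on area if 1 − (1.6/b)² > 0.75, so b > 1.6/0.5 = 3.2 cm. If regression means diameter, 1 − 1.6/b > 0.75, so b > 1.6/0.25 = 6.4 cm. Both lie within the 7 cm limit, the second only narrowly.

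**4. Size per patient.** One reclassified patient moves a rate by 1/77 = 1.3 points (1/85 = 1.2 points if all recruited patients are counted). For scale only: 0, 1, 2 or 4 patients would be 0, 1.3, 2.6 or 5.2 points of 77.

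**5. The effect depends on how the gap is closed.**
- CR at 1.5 cm or less: both 1.5 cm rows above become CR, so each such patient enters the remission rate.
- CRu from 1.5 cm upward: the 4.0 cm case becomes CRu and the 2.5 cm case stays PR. If CRu is not counted as complete remission, the rate does not change.

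Two features of the text favour the first. CRu already starts strictly above 1.5 cm, and the baseline classes (above 1.5 cm; 1.1 to 1.5 cm) put 1.5 cm in the lower class.

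**6. Primary endpoint.** The sample size contains no response term. With 75% against 89%, 95% power and an assumed one-sided alpha of 0.05 (none is stated), N = [(1.645·√(0.75·0.25) + 1.645·√(0.89·0.11)) / 0.14]² = 76.8, or 77 as stated. Nothing in this depends on the 1.5 cm limit.

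**The case against.** The strongest reply is that the bullets condense a cited standard in a journal article. The standard and the full protocol are not at hand, so this may be a slip in summarising and scans may be scored correctly in practice. That is possible, and it limits what can be said about actual scoring. It does not cure the text: the limits are given as explicit numbers, and they do not fit together.

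The other side is also right on several stronger readings that a reader might infer:

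- *That a 1.5 cm residual always scores worse than a 1.6 cm one.* It does so only when the larger residual has regressed by more than 75%. Many smaller nodes show no inversion, though the unassigned value remains.
- *That the small-node limit has the same hole at 1.0 cm.* It does not. No larger small-node residual scores better, so 1.0 cm is just the excluded side of a strict cut-off. Calling that limit wrong would need the cited criteria.
- *That the remission rates are understated by some number of points.* The documents give no node sizes, shrinkage or reading precision. Any simulated figure would rest on assumed distributions and would mostly measure the effect of moving a threshold. Relative to an inclusive CR limit the literal rule can only lower the rate or leave it unchanged, but the article does not say that the inclusive limit is the intended one.
- *That boundary patients are lost from the relapse free survival analysis.* No analysis population for it is stated. Only the relapsed-disease label is closed to them.

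**Conclusion.** The point stands in limited form. As written, a residual of exactly 1.5 cm from a node formerly above 1.5 cm is unassigned between CR and CRu. The response categories are then out of order for baselines above about 3.2 cm (regression on area, proportional shrinkage, 1 mm readings) or above 6.4 cm (regression on diameter).

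The effect is confined to patients whose only obstacle to CR or CRu is a node read at 1.5 cm. It is about 1.3 points per patient of 77, and the number of such patients is unknown. It touches the two complete remission rates and eligibility for the relapsed-disease category. Two-year progression free survival and the 77 evaluable patients are unaffected. This is a small but definite error in a stated rule.

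**What to change.** Reconcile the CR and CRu limits with each other and with the cited response criteria, so that every residual size falls in exactly one category. The simplest closure consistent with the rest of the text is CR at 1.5 cm or less, with CRu left as it is. State whether CRu counts in the complete remission rate. Then apply the settled rule to the recorded diameters at week 7 and week 18.

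The cost is a short wording change and the re-scoring of a few boundary cases. No further scans or patients are needed. With 65 of 85 patients included as of February 2010 (Trial duration), this can be settled before analysis.

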### Quality assurance program

All staging examinations are reviewed centrally as part of the quality assurance program. Completeness of the staging, quality of the imaging and extend of involvement are analysed. In addition, a proposal for the radiation site is sent out to the treatment centre. All radiation treatment plans are also centrally reviewed in a retrospective manner.

## Discussion

The MIR trial is evaluating the effectiveness and the safety of the combination of an involved field radiation therapy with the systemic anti CD20 antibody Rituximab for early stage follicular lymphoma grade 1 or 2 in a multi center setting.. It also might show additional risk factors for a later recurrence (e.g. remission state after Rituximab only).
